## 2. Materials and Methods

We designed a protocol of observational, prospective cohort study according to STROBE statement (see Table S1), in which patients with STEMI will be enrolled [16]. At least 200 consecutive patients who meet inclusion criteria referred to the catheterization laboratory from the Institute of Cardiovascular Diseases “[name]M. Georgescu” will be analyzed. The study protocol was registered in the ClinicalTrials.gov database (NCT05098977) and was approved by the Ethics Committee of the Institute of Cardiovascular Diseases “[name]M. Georgescu” in Iasi, Romania.

Interventional studies involving animals or humans, and other studies that require ethical approval, must list the authority that provided approval and the corresponding ethical approval code.

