### 2.3. HRV Parameters Measured

We will measure HRV parameters recommended by the ESC and the North American Society of Pacing and Electrophysiology guidelines [7]:

(1)Time domain parameters: standard deviation of all NN intervals (SDNN), HRV triangular index, the standard deviation of the average NN interval over short time divisions (SDANN), and the square root of the mean squared differences of consecutive NN intervals (RMSSD);(2)Frequency domain parameters: low-frequency power (LF), high-frequency power (HF), and LF/HF ratio.

Additionally, some nonlinear HRV parameters will be evaluated, such as SD1, SD2, SD2/SD1, approximate entropy, and sample entropy.

HRV will be measured in addition to medical and interventional therapy for myocardial infarction according to the latest ESC guidelines focused on STEMI [2]. HRV will be assessed using a medically approved wrist-wearable device (E4 wristband from Empatica, CE certified) for 5 min segments during myocardial revascularization by primary PCI (before and after revascularization). The E4 device will be placed on the non-dominant hand, with the case tightener on the top of the wrist. The validity of HRV measurement using an Empatica E4 wristband was previously confirmed in a clinical study [13]. Raw data regarding heart rate and HRV (interbeat interval data) will be extracted from the wristband and further analyzed using Kubios software. Among available E4 wristband sensors, photoplethysmography will be used to derive interbeat interval data from blood volume pulse analysis. The blood volume pulse signal has a sampling rate of 64 Hz (resolution 1/64 s) as specified by the manufacturer. All HRV parameters of interest (including frequency domain and nonlinear parameters) will be automatically calculated using Kubios software [18]. Moreover, eventual artifacts in raw data collection will be corrected using a very low threshold algorithm (0.45 s) in Kubios to avoid significant HRV parameters deformation. Additional HRV measurements will be performed after the index event (at one and six months).

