### 2.7. Statistical Analysis

SPSS statistical software version 26.0 will be used (IBM SPSS Statistics, New York, NY, USA). Descriptive statistics will be applied to characterize enrolled patients. Normally distributed data will be represented as mean and standard deviation, while non-normal distributed data will be displayed as median and Inter Quartile Range (IQR). Also, relevant graphics will be used when possible. 

When appropriate, data will be analyzed using parametric (Student’s *t*-test) and non-parametric tests (Mann–Whitney–Wilcoxon). In addition, for statistical hypothesis testing, Student’s *t*-test will be applied in case of continuous variables, while categorical variables will be compared using the chi-square test. Missing data will be handled using a multiple imputation approach.

Odds ratio (OR), corresponding 95% confidence intervals, and p-values will be calculated for each variable related to investigated outcomes. A *p*-value < 0.05 will be considered statistically significant. Univariate logistic regression models will reveal statistically significant variables associated with pre-specified outcomes. Afterward, variables documented as statistically significant in univariate logistic regression models will be included in multivariate analysis. Moreover, the prediction accuracy of time and frequency domain HRV parameters for primary and secondary outcomes will be evaluated using the Receiver Operator Characteristics (ROC) curve. The sensibility, specificity, and c-statistic of individual HRV parameters will be calculated. Additionally, the Kaplan–Meier survival curve will be used to analyze time to event variables.

In addition, the role of HRV parameters for adverse outcomes prediction will be analyzed in three subgroups of high-risk patients, including patients with chronic kidney disease, diabetes mellitus, and elderly participants.

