## 3. Results

In order to enhance the reading process, the results will also be displayed as tables and figures. We will provide data regarding HRV parameters values in patients presenting with STEMI. The correlation between HRV and adverse short- and long-term outcomes will be analyzed and presented. The independent value of HRV measurements for predicting primary and secondary outcomes will also be reported.

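### Selecting the multivariable model by univariable p<0.05, with no confounder forced in, cannot reliably support the promised independent value of HRV

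*Protocol article*

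**What the plan says.** Section 2.7 sets out two steps. First: "Univariate logistic regression models will reveal statistically significant variables associated with pre-specified outcomes". Then: "variables documented as statistically significant in univariate logistic regression models will be included in multivariate analysis". The threshold in the same section, referring to p, is "value < 0.05 will be considered statistically significant". The screen is broad, since odds ratios "will be calculated for each variable related to investigated outcomes". The section names no covariate that must stay in and no limit on the number of terms.

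Section 2.3 supplies the HRV candidates: four time-domain measures, three frequency-domain measures ("low-frequency power (LF), high-frequency power (HF), and LF/HF ratio") and five named nonlinear ones ("such as SD1, SD2, SD2/SD1, approximate entropy, and sample entropy"). That makes 12, each recorded before and after revascularisation. Section 2.4 lists roughly 30 clinical, laboratory and angiographic variables, including the GRACE score and LVEF.

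The sample, in Section 2, is "At least 200 consecutive patients who meet inclusion criteria". Section 3 states the inference to be drawn: "The independent value of HRV measurements for predicting primary and secondary outcomes will also be reported".

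**The concern.** To call HRV an independent predictor is to say that it adds information once the established predictors are accounted for. Under the Section 2.7 rule, the established predictors are whichever ones reached p<0.05 in this dataset. With few events, a moderate confounder can easily miss that threshold. HRV is then adjusted for too little and can look independent because it carries the omitted confounder's effect. HRV itself also enters only when its own estimate is large enough to be significant, and the final model takes no account of that selection.

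The rule can also give a different adjustment set for each outcome and each of the three evaluation times in Section 2.5, so the adjusted HRV results would not be comparable with one another. At stake is the adjusted claim behind the article's stated ambition, in the Abstract and Section 5, of bringing HRV into future risk scores and guidelines.

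**Working it through.** The plan has no figure of its own to reproduce here. The inputs are:

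- N = 200, the minimum in Section 2.
- Screening level 0.05 (Section 2.7), taken as two-sided because the text does not say.
- Event rate r: not in the document. Assumed 10% and 20%, i.e. 20 and 40 events; 5% (10 events) is a sensitivity case.
- Effect sizes: OR 1.5 per SD for a moderate predictor (assumption). OR 1.46 per SD for HRV, borrowed from the HR for adverse cardiovascular events in the meta-analysis described in Section 4 (treating it as an OR per SD is an assumption).

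**Step 1, size of the pool.** Twelve HRV parameters plus about 33 clinical variables (a count of the Section 2.4 list) give about 45 candidates. Events per candidate are 20/45 = 0.4 and 40/45 = 0.9. Counting both index recordings adds 12 more candidates.

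**Step 2, chance that a real confounder misses the screen.** SE of the log OR per SD is 1/√(N·r·(1−r)).

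- 20 events: SE = 1/√18 = 0.236. ln 1.5 = 0.405, so z = 0.405/0.236 = 1.72. Pass probability is Φ(1.72 − 1.96) = 0.41, so it misses 59% of the time.
- 40 events: SE = 1/√32 = 0.177, z = 2.29. Pass probability is Φ(2.29 − 1.96) = 0.63, so it misses 37%.
- 10 events: the same formula gives a 76% miss.
- A strong predictor (OR 2.52 per SD) misses only 2% of the time at 20 events and essentially never at 40.

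**Step 3, exaggeration of one univariable estimate that passes.** The mean log OR given selection is b + SE·φ(1.96 − b/SE)/P(pass).

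- 20 events: 0.405 + 0.236 × 0.388/0.405 = 0.631, i.e. OR 1.88. On the log scale, 0.631/0.405 = 1.56 times the truth.
- 40 events: 0.405 + 0.177 × 0.377/0.631 = 0.511, i.e. OR 1.67, or 1.26 times the truth.

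**Step 4, the whole two-step rule with one HRV index.** Simulation with N = 200, five true confounders (OR 1.5 per SD, each correlated 0.25 with HRV), 18 noise variables and 1,500 runs per scenario. The comparator is a pre-specified model with HRV and all five confounders.

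| Quantity | 20 events | 40 events |
|---|---|---|
| HRV falsely independent (true OR 1.00) | 13% | 11% |
| Median adjusted OR when HRV is selected, truth 1.00 | 1.49 | 1.27 |
| Median adjusted OR when HRV is selected, truth 1.46 | 1.84 | 1.67 |
| Pre-specified model, median OR, truth 1.00 | 0.99 | 1.00 |
| Pre-specified model, median OR, truth 1.46 | 1.50 | 1.50 |

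A second simulation with one index and three moderate confounders agrees. False independent findings came to about 10%, against about 5% for a pre-specified model. The adjusted OR among selected runs was 1.53 and 1.29 when the truth was 1.00, and coverage of the 95% interval after selection was 64% to 78% under the null.

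**Step 5, with 12 correlated HRV indices** (600 runs per scenario, event rates 5% to 20%).

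- At least one of the five true confounders was dropped in 93% to 100% of runs.
- The model kept 4 to 14 terms, with 1.4 to 4.3 events per retained term.
- HRV was falsely declared independent in 10% to 13% of runs. With one index pre-specified, the figure was about 4% to 6%.
- The apparent c-statistic was 0.77 to 0.87, against 0.61 to 0.70 in new data.
- With a true HRV log OR of 0.38, the median for a selected index was 0.35 to 0.39, so there was no clear inflation of single coefficients.

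**The case against.** The strongest reply has four parts.

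First, a reader might infer that the adjusted HRV effect will always be biased away from the null. The material does not support that. The 1.88 and 1.67 in step 3 are univariable estimates for a single index. Inflation of the adjusted OR was shown only when one index is in play; with 12 correlated indices the coefficients are unstable instead. This part stands and limits the claim.

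Second, a reader might infer that adjustment for GRACE or LVEF is a matter of luck. The article gives no effect size for either, and step 2 shows that a very strong predictor would usually survive. Chance omission is a problem for moderate confounders. This also stands. It does not rescue the rule, because nothing in it guarantees that any given confounder stays.

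Third, Section 2.4 is a data-collection list, and Section 2.7 does not say that only screened variables may enter. True, but the screen is the only route into the model that the section describes, and its reference to each variable is broad. This is a rule the article fixes, not detail left to an analysis plan.

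Fourth, the study is observational, and the ROC and Kaplan–Meier analyses do not pass through the screen. That is correct. As Section 2.7 describes them, however, they are not adjusted, so the independent value promised in Section 3 has to come from the multivariable model.

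**Conclusion.** The point holds. Univariable screening at p<0.05 without forced confounders is not a reliable basis for an independent-value claim in a cohort of this size. At an assumed 20 to 40 events, a confounder with OR 1.5 per SD is missed about 59% to 37% of the time, and HRV is falsely declared independent in roughly 10% to 13% of simulated runs instead of 5%. With one HRV index, its OR is also exaggerated, both univariably and after adjustment. With many correlated indices, the harm is instability, lost confounders and over-optimistic discrimination.

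The sizes rest on the assumed event rate, on N = 200 (the article says at least 200), and on the simulated strength and correlation of the confounders. Across the 5% to 20% range, the loss of moderate confounders and the excess of false findings kept the same direction. Unscreened measures of HRV, such as its c-statistic, are not affected by this point.

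**What to change.** For the 1-year primary outcome, replace the screening rule with one model fixed before outcome data are examined:

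- One named HRV parameter at one named time point (before or after revascularisation).
- A short forced clinical set, for example GRACE, with LVEF and heart rate if events allow. These are already collected under Sections 2.3 and 2.4.
- All terms kept whatever their p-values.
- The number of terms set by the number of events, with the order of entry of covariates written down in advance. Taking 10 events per parameter as a working assumption, 20 events carry 2 terms (HRV and GRACE) and 40 carry 4. A four-term model is therefore itself tight at 20 events.
- Penalised estimation (Firth or ridge) by default.

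Report the univariable results as descriptive and the other HRV parameters as exploratory.

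The cost is a change of wording, with no new data. The price is fewer covariates in the final model and probably a less favourable apparent HRV effect.

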### 2.5. Outcomes and Follow-Up

The primary composite outcome will include all-cause mortality and major adverse cardiovascular events (MACE). MACE will include cardiac mortality, fatal and non-fatal myocardial infarction, unplanned target vessel revascularization (TVR), and stroke (ischemic or hemorrhagic).

In addition, several secondary outcomes will be analyzed: (a) all-cause and cardiac mortality; (b) fatal and non-fatal myocardial infarction; (c) unplanned target vessel revascularization; (d) target lesion revascularization (TLR); (e) stroke; (f) hospitalizations for heart failure; (g) ventricular arrhythmias; (h) LVEF and left ventricular diastolic function. Moreover, the primary composite outcome will be evaluated in a high-risk subgroup of patients, such as elderly patients or those with diabetes mellitus/chronic kidney disease.

TVR will be defined as new stenosis requiring PCI or CABG in another part of the coronary artery treated at the index event. TLR will include unplanned PCI or CABG for the same lesion revascularized during primary PCI. LVEF will be measured using two-dimensional transthoracic echocardiography (Simpson methods). At least E/A or E/e prime ratios will be calculated for left ventricular diastolic function. Ventricular arrhythmias will be defined as ventricular fibrillation or sustained ventricular tachycardia documented at electrocardiographic monitoring. The primary composite outcome and secondary outcomes will be evaluated during the hospital stay, at 1 month and 1 year following admission for STEMI. All data regarding the outcomes will be collected from secure medical records.

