## 4. Discussion

Our study will prospectively investigate the impact of HRV time domain, frequency domain and nonlinear parameters on adverse outcomes in a contemporary cohort of STEMI patients revascularized by primary PCI. To the best of our knowledge, it will be the first study to document the potential prognostic role of HRV variables in STEMI patients measured with a wrist-wearable medical device.

HRV represents an indirect marker of autonomic nervous system function, reflecting the impact of sympathetic and parasympathetic nervous systems balance on the heart [19]. HRV constitutes not only the result of a complex connection between the central nervous system and the heart, but also an active marker that can be enhanced [20]. In this regard, HRV could be influenced by a unique respiration technique, HRV biofeedback, which could improve outcomes in various chronic conditions, including cardiovascular diseases [21]. As we have previously shown, this bidirectional interaction is a dynamic process, while modulating HRV could have favorable implications on STEMI end points [22].

Consequently, this expression of heart–brain interaction could represent a prognostic marker in patients with cardiovascular diseases [23]. A meta-analysis on 28 cohort studies involving patients with cardiovascular diseases reported that HRV parameters (both time- and frequency domain variables) were significantly associated with all-cause death (HR 2.12, 95% CI, 1.64–2.75) and adverse cardiovascular events (HR 1.46, 95% CI, 1.19–1.77). Interestingly, in a subgroup analysis, HRV values were only correlated with all-cause death in the case of patients with AMI (HR 2.52, 95% CI, 1.75–3.62), but not in those with heart failure (HR 1.47, 95% CI, 0.99–2.17) [24]. However, studies that enrolled AMI patients are old and did not reflect current treatment options and guidelines. As a consequence, the impact of HRV measurement in contemporary patients with STEMI should be reassessed.

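### Kaplan-Meier is named for every time-to-event outcome, so curves for secondary outcomes that leave out all-cause death would slightly overstate 1-year incidence

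*Protocol article*

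**What the plan says.** Section 2.7 of the protocol article ends its description of the main analyses with this sentence: "Additionally, the Kaplan–Meier survival curve will be used to analyze time to event variables". It lists no outcomes, makes no exception and names no other time-to-event method.

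Section 2.5 defines the outcomes. For the primary one: "The primary composite outcome will include all-cause mortality and major adverse cardiovascular events (MACE"). The secondary list opens with all-cause and cardiac mortality and with fatal and non-fatal myocardial infarction, and continues: "c) unplanned target vessel revascularization; (d) target lesion revascularization (TLR); (e) stroke; (f) hospitalizations for heart failure; (g) ventricular arrhythmias". It closes with ejection fraction and diastolic function, which are not time-to-event outcomes. Primary and secondary outcomes are assessed in hospital, at 1 month and at 1 year.

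The association and prediction analyses rest on other methods. Section 2.7 says "Univariate logistic regression models will reveal statistically significant variables associated with pre-specified outcomes", with a multivariate model to follow, and says that prediction accuracy "for primary and secondary outcomes will be evaluated using the Receiver Operator Characteristics (ROC) curve".

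**The concern.** Kaplan-Meier recognizes two statuses, event or censored, and reads censoring as though the patient could still have the event later. Where all-cause death is part of the outcome, this causes no difficulty. Where it is not, a patient who dies without the event can no longer have it, yet is censored. The curve then spreads that patient's future risk over the survivors, and 1-KM estimates incidence in a hypothetical population in which nobody dies first.

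Seven clinical secondary outcomes are exposed: cardiac mortality (through non-cardiac death), myocardial infarction, unplanned target vessel revascularization, target lesion revascularization, stroke, heart failure hospitalization and ventricular arrhythmias. At stake is the 1-year incidence read from their curves. The article expects HRV to predict death and cites a meta-analysis in which "HRV values were only correlated with all-cause death in the case of patients with AMI (HR 2.52, 95% CI, 1.75–3.62"). If curves were drawn by HRV level, the overstatement would therefore differ between the groups.

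**Working it through.** **Stated figure.** The article gives no mortality, incidence, event count or power, so there is no planned figure to reproduce. From the article: at least 200 patients (Section 2), 1-year follow-up (Section 2.5), and hazard ratios of 2.52 for death in AMI and 1.46 for adverse cardiovascular events (Section 4, from the cited meta-analysis). All event and death rates below are assumptions.

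**Check 1: constant hazards.** Let k be the 1-year risk read from Kaplan-Meier with deaths censored, and d the 1-year risk of death. Then a = -ln(1-k), b = -ln(1-d), and the cumulative incidence is CIF = a/(a+b) × (1 - exp(-(a+b))).

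With k = 10%, a = 0.1054.
- d = 3%: b = 0.0305, CIF = 9.85%, overstatement 0.15 points.
- d = 5%: b = 0.0513, CIF = 9.75%, overstatement 0.25 points.
- d = 10%: b = 0.1054, CIF = 9.50%, overstatement 0.50 points.
- d = 20%: CIF = 8.98%, overstatement 1.0 point.

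The upper bound puts every death before any event, so CIF = (1-d) × k. At d = 5% this gives 9.5% (0.5 points), and at d = 10% it gives 9.0% (1.0 point).

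**Check 2: deaths clustered early.** Assume that 60% of 1-year deaths fall in the first 30 days and that events start after day 7. In daily steps over 365 days, solve the event hazard so that the cumulative incidence equals the stated value, then compute 1-KM. The standard error is sqrt(p(1-p)/n) with n = 200.

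| Mortality | True incidence | 1-KM | Overstatement (points) | Standard error (points) | Ratio |
|---|---|---|---|---|---|
| 5% | 8% | 8.3% | 0.32 | 1.92 | 0.17 |
| 10% | 10% | 10.8% | 0.83 | 2.12 | 0.39 |
| 12% | 12% | 13.2% | 1.22 | 2.30 | 0.53 |

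**Check 3: if curves were split by HRV.** Use constant hazards and a reference group with d = 5% and k = 10%. Applying the two cited hazard ratios to the low-HRV group:
- death risk = 1 - 0.95^2.52 = 12.1%;
- Kaplan-Meier event risk = 1 - 0.90^1.46 = 14.26%, with CIF = 13.40%.

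The overstatement is 14.26 - 13.40 = 0.86 points in the low-HRV group and 10 - 9.75 = 0.25 points in the reference group. The gap between groups is 4.26 points by Kaplan-Meier and 3.64 points by cumulative incidence. With an assumed 100 patients per group, the standard error of the Kaplan-Meier difference is sqrt(0.10×0.90/100 + 0.1426×0.8574/100) = 4.6 points. The distortion of about 0.6 points is well inside sampling error.

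**Check 4: logistic and ROC analyses.** These score a patient who dies without the event as a non-event at 1 year. With complete follow-up, the proportion with the event is then the 1-year absolute risk, which is what the cumulative incidence function estimates. They do not share the Kaplan-Meier problem.

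**The case against.** The strongest reply is that the sentence on Kaplan-Meier lists no outcomes and states no censoring rule. It could be meant only for the primary composite and all-cause death, and a condensed article may leave endpoint-level detail to a fuller document. It is true that no censoring rule is written. But the sentence fixes a method for time-to-event variables without exception, Section 2.5 lists several that leave out all-cause death, and for those the method has no way to handle a death except to censor it. The point concerns a stated method, not a missing detail.

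The reply is right about size. Kaplan-Meier is an added analysis, and the early-death pattern in Check 2 is an assumption that the article does not supply.

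A reader might infer three stronger conclusions, which the article does not support.
- *That the planned HRV comparison is biased.* Section 2.7 sets no HRV cut-off and plans no Kaplan-Meier comparison by HRV. Check 3 is conditional on such a split.
- *That the high-risk subgroup results are biased.* Section 2.5 assigns these subgroups the primary composite, which includes death. Section 2.7 speaks more broadly of predicting adverse outcomes in "three subgroups of high-risk patients, including patients with chronic kidney disease, diabetes mellitus, and elderly participants", but names no method there. Subgroup sizes and mortality are not given either.
- *That logistic regression and ROC are distorted by counting the dead as event-free.* Check 4 shows that they target the same absolute risk as the recommended estimator. A c-statistic computed without those patients would answer a different question.

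**Conclusion.** The point holds for the secondary time-to-event curves only. Applied as written, Kaplan-Meier would overstate the 1-year incidence of outcomes that do not include all-cause death. The direction is certain whenever some patients die without the event while others are still at risk and later have it. The size rests on assumed rates: about 0.3 to 1.2 points for whole-cohort mortality of 5% to 12% with early deaths, and 0.25 to 0.5 points for mortality of 5% to 10% under constant hazards with a 10% event risk. At 200 patients the early-death figures are below, or about, half a standard error. The excess grows with mortality and would be unequal between HRV groups if curves were split that way and low HRV predicts death. The primary composite, all-cause death, and the logistic and ROC results are unaffected. This is a cheap improvement, not a threat to the study's main conclusions.

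**What to change.** In Section 2.7:
- Restrict Kaplan-Meier to the primary composite and all-cause death.
- For the other clinical outcomes, use the Aalen-Johansen cumulative incidence function with death without the event as the competing event. For cardiac mortality, the competing event is non-cardiac death.
- If HRV groups are compared on these outcomes, use Gray's test or a cause-specific hazard ratio.

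No new data are needed, and the logistic and ROC analyses stay as they are. The cost is a few words and a routine analysis; SPSS 26 may need an R extension or other software. Reported incidences for these outcomes become slightly lower. The choice should be written down before the curves are seen.
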